**LIST OF ABBREVIATIONS AND RELEVANT DEFINITIONS**

| **WBS** | **Whole body scan** |
| --- | --- |
| **Dx** | **Diagnostic** |
| **ICRP** | **International Commission on Radiological Protection** |
| **GBq** | **GigaBecquerel** |
| **RIVM** | **Rijksinstituut voor Volksgezondheid en Milieuhygiëne** |
| **CV** | **Curriculum Vitae** |
| **IC** | **Informed Consent** |
| **IMPD** | **Investigational Medicinal Product Dossier** |
| **METC** | **Medical Research Ethics Committee (MREC); in Dutch: Medisch Ethische Toetsingscommissie (METC)** |
| **(S)AE** | **(Serious) Adverse Event** |
| **Wbp** | **Personal Data Protection Act (in Dutch: Wet Bescherming Persoonsgevens)** |
| **WMO** | **Medical Research Involving Human Subjects Act (Wet Medisch-wetenschappelijk Onderzoek met Mensen** |
| **Sponsor** | **The sponsor is the party that commissions the organization or performance of the research, for example a pharmaceutical company, academic hospital, scientific organization or investigator. A party that provides funding for a study but does not commission it is not regarded as the sponsor, but referred to as a subsidizing party.** |
| **DTC** | **Differentiated thyroid carcinoma** |
| **Tg** | **Thyroglobulin** |
| **rhTSH** | **recombinant human Thyrotropin Stimulating Hormone** |
| **US** | **Ultrasound** |
| **mCi** | **milliCurie** |
|  |  |
|  |  |

**SUMMARY**

**Rationale**

Patients with differentiated thyroid cancer (papillary and follicular) are treated with near-total thyroidectomy. In most of the patients this treatment has to be followed by ablation with I-131 to eliminate remnant thyroid tissue to decrease the risk of tumor recurrence and improve sensitivity and specificity of Tg measurement in follow-up. With the introduction of rhTSH the question arises, whether ablative therapy after pretreatment with rhTSH during euthyroidism can be used instead of the classical way of inducing hypothyroidism by withholding suppletion which induces endogenous rise of the TSH level.

**Objectives**

To determine the rate of ablation failure in differentiated thyroid cancer patients using rhTSH instead of thyroid hormone withdrawal for stimulation of remnant tissue, using a fixed dosage of 3.7 GBq (100 mCi).

**Study design**

Prospective multicenter study in the Netherlands.

**Study population**

The maximum number of patients will be 144.

**Intervention (if applicable)**

Two rhTSH injections will be given 6 weeks after total thyroidectomy (before I-131 treatment) and 9 months after the first high dosage I-131treatment.

**Main study parameters/endpoints:**

The primary endpoint of successful ablation is defined as: rhTSH Tg < 1ng/ml, negative rhTSH dxWBS, negative neck US and negative Tg antibodies. If a second (blind) I131 treatment is necessary, according to the Dutch guidelines) the definition of successful ablation is defined as no visible uptake in the original thyroid bed on a post therapeutic scintigraphy.

**Nature and extent of the burden and risks associated with participation, benefit and group relatedness:**

Use of radioactivity means exposure to ionizing radiation. Standard clinical I-131dosage will be given (orally) to patients. Thus, patients will not be exposed to extra radiation. Moreover, I-131 will be cleared more easily when patients are euthyroid instead of hypothyroid, so the radiation burden will decrease.

# INTRODUCTION AND RATIONALE

Patients with differentiated thyroid cancer (papillary and follicular) are treated with near-total thyroidectomy. In most of the patients this treatment has to be followed by ablation with I-131 to eliminate remnant thyroid tissue to decrease the risk of tumor recurrence and improve sensitivity and specificity of Tg measurement in follow-up. With the introduction of rhTSH the question arises, whether ablative therapy after pretreatment with rhTSH during euthyroidism can be used instead of the classical way of inducing hypothyroidism by withholding suppletion which induces endogenous rise of the TSH level.

Several studies have been published about the use of rhTSH preceding I-131 ablation therapy. In two studies a low standard ablation dosage was used after stimulation with rhTSH (30 mCi).1, 2 A prospective ablation study in 64 patients from 9 international centers compared the rhTSH pretreatment during thyroxin treatment and thyroxin withdrawal after a high dosage of 100 mCi.3 Primary endpoint of the study was the rhTSH stimulated I-131 uptake in the thyroid bed after eight months. The statistical basis of this last mentioned study was based on a non-inferiority framework that was not optimally performed because of a small group size of 21 and 24 patients in both arms. Although the authors reached a different conclusion, this study lacks power and only demonstrates that the two strategies are comparable when a successful ablation rate of 73% is considered acceptable. With this (very liberal) assumption a comparable success of ablation was found with regard to the local thyroid bed. However, this only implicates that an ablation failure rate of 27% is considered ‘non inferior’ to the rate of 7% unsuccessful ablations in the standard endogenous rise of TSH. Recently an update of these patients and no differences have been found in the success of thyroid remnant ablation therapy or clinical outcomes between endogenous TSH stimulation by withholding thyroid hormone therapy vs. exogenous TSH in the euthyroid state in low-risk patients after a median follow-up of 3.7 yr.4

A recently published retrospectively rhTSH-assisted remnant ablation had shown similar rates of clinically evident disease recurrence and persistent uptake in the thyroid bed as with the traditional thyroid hormone withdrawal.5

Despite these difficulties in the statistical proof of non-inferiority, the potential short-term benefits of rhTSH for the patients with regards to quality of life and socio-economic factors (in medical factors and missed work time) are unequivocal 6and make the application of rhTSH attractive. Also whole body radiation is lower after rhTSH stimulation for renal clearance of I-131 is not decreased by hypothyroidism, resulting in a lower total body radiation. A more definitive proof, by prospective studies, that such a strategy is not ultimately harmful to patients, however, is desirable.

The above mentioned discussion has resulted in a recommendation in the Dutch guidelines for the treatment of thyroid cancer that withdrawal of thyroid hormone as well as rhTSH can be used for the ablation therapy (www.oncoline.nl).

Another point of discussion is the optimal activity dosing of radioactive iodine for ablation therapy. In a systematic review of Hackshaw 7 various dosage activities of radioactive iodine were compared, by pooling data of observational studies. It was concluded that ablation success was significantly higher by using 100 mCi compared with 30 mCi. However, these findings could not be confirmed in a pooled analysis of randomized controlled trials. A subsequent single-center randomized controlled trial with 72 patients showed that short term rhTSH ablation success were the same (89%) using 50 or 100 mCi radioactive radioiodine.8 Although this point needs further clarification, in the currently proposed study we address the question that the ablation using rhTSH pre-treatment is safe in a prospective study.

# OBJECTIVES

**Primary Objective**

To determine whether the failure rate of the I-131 ablation therapy after rhTSH stimulation is equal to the failure rate of I-131 therapy after endogenously stimulated I-131 ablation and using a fixed dosage of 3.7 GBq (100 mCi).

# STUDY DESIGN

Multicenter study in the Netherlands.

A conventional design would be to perform a randomized study comparing TSH preparation with endogenous TSH rise. However, the disadvantage of a randomized study is the tremendous number of patients needed, which is calculated to be 552 patients (based on an acceptable ablation failure rate of 10% versus an alternative hypothesis of 20%, power 90%, alpha 0.05). In addition, even after having performed a randomized study, the main question remains whether the ablation failure rates in the rhTSH arm would be acceptable for widespread application. For example, a statistically higher failure rate after rhTSH could still be considered clinically acceptable.

Therefore, to confirm that the efficacy of rhTSH pre-treatment for ablation therapy is not inferior to withdrawal of thyroid hormone, a fully sequential design will be used, with preset boundaries for stopping in case of inferiority or equality of the rhTSH strategy.

If the failure score by rhTSH passes the upper boundary of the acceptable failure rate then rhTSH is considered inferior to the conventional withdrawal ablation. If failure score after rhTSH passes the lower boundary than rhTSH stimulation is at least equal. This design is less conventional, but is expected to grow significantly in medical research as it provides very clear answers, without the need to confirm what is already known over and over (as is the case in the standard arm of a RCT). 9 (See also statistical analysis)

This is a prospective observational study and a fully sequential design will be used, with preset boundaries for stopping in case of inferiority or equality of the rhTSH strategy.

All patients will be treated according protocol using rhTSH (Dutch guidelines). All scan and laboratory evaluation together the treatment decision will be executed in the participating centers. Scans and blood for central reading will be collected and re-evaluated in Groningen every 4 months. This re-evaluation is the study evaluation and will not change the standard treatment.

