# STUDY POPULATION

# Population (base)

The maximum number of patients will be 144 (constant alpha=0.014, cumulative alpha=0.05; beta =0.10). This means that with a true failure rate of 10%, the probability of passing the upper boundary is below 5%, with a power of 90%. It is expected that the patients will be recruited within a period of 2 years in the above mentioned centers.

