# STATISTICAL ANALYSIS

# Descriptive statistics

**Power analysis**

Data on ablation rates.

Based on literature and local Dutch data the investigators agree that a mean ablation failure rate up to 10% is considered acceptable.

Definition of ablation success : A recent review has analyzed the success rate of ablation at 80% with 100mCurie after withdrawal.7 Results from Dutch centers vary from 88% , 93% and lower (68% and 86%) and 56%.13-15

A historical ablation success rate defined on the basis of the post therapeutic scan in those patient with a second blind I131 therapy will follow.

Event = ablation failure as defined above

Event =

ablation failure as defined above

Figure 1

*Background of the sequential design with stopping rule*

A sequential design with a stopping rule equipped with two boundaries, gives the opportunity to use every single consecutive ablative therapy in a daily executed interim analysis.(see fig.1)

The preset upper boundary allows premature stopping in case of an observed failure rate that is inferior to the acceptable rate of 10%, with a rate of 20% as alternative ( Total maximal number of patients 144; constant alpha=0.014, cumulative alpha=0.05; beta =0.10). This means that with a true failure rate of 10%, the probability of passing the upper boundary is below 5%, with a power of 90%.

The preset lower boundary allows premature stopping for futile testing (constant alpha=0.2638, cumulative beta=0.10; cumulative alpha=0.05). This means that with a true failure rate of 20%, the probability of passing the lower boundary is below 10% and that the probability of subsequent passage of the upper boundary would be below 5%.

The 50% probability of stopping (because of passing the upper or lower boundary) in case of a 20% failure rate is reached within the first 50 consecutive patients, whereas the 50% probability of stopping in case of a 10% failure rate is reached within 77 patients.

During the study, there is an analysis after entering each new patient. When the lower boundary is passed, sequential monitoring can be stopped, interim statistical analysis will be done and the use of rhTSH will become the standard treatment. Final statistical analysis will be done after completion of all 144 patients.

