When the upper boundary is passed, the study will be stopped prematurely and the use of rhTSH (with dosage and timing as in the protocol) can not become the standard treatment. Final statistics will be provided. Then two alternatives can be followed: withdrawal remains the standard treatment or a new study is started with different time and/or dosing of rhTSH.

The probabilities of stopping with various true failure rates are given in figure 2.

Figure 2 Probability of stopping at different failure rates 5 -25%

*Stopping rule with two boundaries*

*The upper boundary*

For one group of patients we can investigate inferiority of the failure rate p to H0: p<=p0 with the alternative H1:p>=p1. With a fully sequential design an upper boundary UB(n) can be constructed, being the maximally accepted number of events within n consecutive patients.

If the failure rate is p, then P(p,n-1,UB(n-1)) is the probability that the number of failures after (n-1) patients is UB(n-1). When the chosen one-sided level of significance is alpha(n-1), then P(p,n-1,Ub(n-1))>= alpha(n-1). Also alpha(n) has been chosen. In case an event occurs in patient n, there are two possibilities:

1) (P(p,n-1,UB(n-1)))*p=P(p,n,UB(n-1)+1)<alpha(n). This would mean that this result

is unacceptable, activating the stopping rule. Thus the upper boundary has been

passed, making UB(n-1)=UB(n). The probability of passage is P(p,n,UB(n)+1).

2) (P(p,n-1,UB(n-1)))*p=P(p,n,UB(n-1)+1)>=alpha(n). This would mean that this

result is acceptable, leaving the stopping rule inactivated. The upper boundary is

not passed, making UB(n)=UB(n-1)+1. The probability of passage is

P(p,n,UB(n)+1)=0.

The cumulative probability P(sum UB) to pass the upper boundary is the sum of P(p,n,UB(n)+1) from n=1 to n=N. N is the maximum of patients needed.

For p=p0 P(p0,sum UB) should not exceed a chosen value of alpha(rule). And for p=p1 P(p1,sum UB) should exceed a chosen value of (1-beta(rule)), being the power.

In this way the upper boundary serves as a fully sequential test of inferiority. When the boundary is passed, we do not accept H0 and declare the failure rate inferior to p0.

*The value of alpha(n).*

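### The boundaries test the rhTSH failure rate against a fixed 10%, but the primary objective and both boundary conclusions are worded as comparisons with withdrawal

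*Protocol*

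**What the plan says.** **Comparative wording.** The Primary Objective is to determine whether failure after rhTSH "is equal to the failure rate of I-131 therapy after endogenously stimulated I-131 ablation". Study Design says the aim is to confirm that rhTSH is not inferior to withdrawal, and twice describes the boundaries as stopping for inferiority or equality. If the upper boundary is passed, "then rhTSH is considered inferior to the conventional withdrawal ablation". If the lower one is passed, rhTSH is taken to be at least equal.

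**What is tested.** Study Design has every patient treated with rhTSH and explains why no randomised control is used. The statistical section describes a one-group test: "For one group of patients we can investigate inferiority of the failure rate p to H0: p<=p0 with the alternative H1:p>=p1". The null rate is set by agreement: "Based on literature and local Dutch data the investigators agree that a mean ablation failure rate up to 10% is considered acceptable". The upper boundary is for a rate "inferior to the acceptable rate of 10%, with a rate of 20% as alternative". The description of the upper boundary gives its result as a failure rate inferior to p0. It does not mention withdrawal there.

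**Withdrawal rates cited.** The Introduction gives 7% unsuccessful ablations with endogenous TSH rise, from a prospective comparison at 100 mCi. The Power analysis says: "A recent review has analyzed the success rate of ablation at 80% with 100mCurie after withdrawal", which is 20% failure.

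**The concern.** A test against a constant can only give a conclusion about that constant. It becomes a conclusion about withdrawal only if the constant is the withdrawal failure rate on the same endpoint, and the protocol does not show that it is. It presents 10% as an acceptable rate, and the two rates it explicitly ties to withdrawal lie either side of it, at 7% and 20%. The higher one coincides with p1.

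The wording matters because the verdict has consequences. Under Premature termination and the Power analysis, passing the lower boundary makes rhTSH the standard treatment, and passing the upper one rules that out. A reader told that rhTSH is inferior or at least equal to withdrawal would take it that the two had been compared.

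**Working it through.** **Inputs.** p0 = 0.10, p1 = 0.20, N = 144, constant alpha 0.014 for the upper boundary and 0.2638 for the lower one (Population and Power analysis). The boundary formulas are those printed in the statistical section.

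**Boundaries.**
- Z(1 − 0.014) = 2.197 and Z(1 − 0.2638) = 0.632.
- UB(n) = integer{0.1n + 2.197·√(0.1n) + 1}. At n = 144: 14.4 + 8.34 + 1 = 23.74, so UB(144) = 23.
- LB(n) = integer{UB(144) + 1 − 0.2(144 − n) − 0.632·√(0.2(144 − n))}, not below 0. At n = 144 this is 24. It first exceeds 0 at n = 44: 24 − 20 − 2.83 = 1.17, so LB(44) = 1.
- The trial stops high when failures exceed UB(n) and low when they fall below LB(n). Because LB(144) = UB(144) + 1, every path ends at one boundary.

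**Method.** Exact patient-by-patient binomial recursion with both boundaries active.

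**The plan's own figures first.**

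| Quantity | Stated | Recomputed |
|---|---|---|
| Pass upper, true rate 10% | below 5% | 5.1% |
| Pass upper, true rate 20% | 90% | 89.9% |
| Pass lower, true rate 20% | below 10% | 10.1% |
| 50% stopped, true rate 20% | within 50 patients | patient 50 |
| 50% stopped, true rate 10% | within 77 patients | patient 76 |

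The design reproduces. The excess over 5% is rounding of the constant alpha (0.0135 to 0.0139 gives 4.97% to 4.98%) and is not a finding.

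**Same recursion at the rates the protocol ties to withdrawal.** Suppose rhTSH has exactly the withdrawal failure rate, so that inferior is the wrong verdict.

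| Withdrawal rate = rhTSH rate | Called inferior | Called at least equal |
|---|---|---|
| 7% (Introduction) | 0.7% | 99.3% |
| 20% (review, Power analysis) | 89.9% | 10.1% |

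On the second line, the chance of the wrong verdict is the design's stated power.

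**The opposite error.** If withdrawal fails in 7% and rhTSH in 10%, rhTSH is worse by 3 percentage points. The lower boundary is then passed with probability 94.9%, and the verdict reads at least equal.

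**The case against.** A single-arm test against an agreed acceptable rate is a legitimate design. Study Design says that acceptability is the main question and that a statistically higher failure rate could still be clinically acceptable. The Power analysis and the upper-boundary description word the test correctly, and a high probability of rejecting at 20% is what the hypotheses intend. All of this stands, and it defends the boundaries. It does not defend the comparative wording: if a higher rate than withdrawal can be acceptable, then acceptable and not inferior to withdrawal are different claims.

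Three stronger readings are tempting and are not supported:

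- **That 20% is the protocol's withdrawal rate, so a false verdict of inferiority is nearly guaranteed.** The protocol does not rank its sources, and the 7% is just as explicitly tied to withdrawal. Nor does it say how the review defined success, and the 7% comes from a study judged on the thyroid bed, whereas this trial uses a four-part composite. The 90% holds only on condition that withdrawal fails in 20% on this endpoint.
- **That the Dutch centre results can be averaged into a withdrawal rate.** They are given without preparation, activity, endpoint or denominators, and one of the references cited for them compares uptake-related with fixed-dose strategies. No figure here rests on them.
- **That the absence of a control arm is itself an error.** The protocol gives its reasons, and the fault lies in what is concluded.

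**Conclusion.** The point holds as an inconsistency between the conclusions and the test. The rule answers whether rhTSH failure exceeds a pre-set 10%; the Primary Objective and Study Design report the answer as equality, non-inferiority or inferiority to withdrawal. The size of the possible error depends on a withdrawal rate that the protocol does not fix. Over the two rates it labels as withdrawal, a false verdict of inferiority has probability between 0.7% and about 90%. In the other direction, a 10% rate against a 7% withdrawal rate is called at least equal in about 95% of trials.

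These figures assume the boundaries as printed, independent outcomes, and a withdrawal rate measured on this trial's endpoint. The wording conflict needs none of these assumptions.

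**What to change.** In the Primary Objective and Study Design, state the objective and both conclusions as: *the failure rate with rhTSH does / does not exceed the pre-set acceptable rate of 10%*. This matches the statistical section. In those two places, delete the claims of equality, of non-inferiority to withdrawal, of inferiority to conventional withdrawal, and of being at least equal. The objective in the Summary asks only for the rate of ablation failure and needs no change.

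Passing the lower boundary means accepting H0, so report the rule's error rates beside that conclusion: 5% at a true rate of 10%, and 10% at a true rate of 20%.

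The cost is a change of wording and a narrower claim. The boundaries, the maximum of 144 and the conduct of the study stay as they are, and no extra patients are needed.

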## Premature termination of the study (see Statistical Analysis, page 14)

During the study every 3 months evaluation will take place of scans and laboratory measurements. When the lower boundary is passed, sequential monitoring can be stopped, interim statistical analysis will be done and the use of rhTSH will become the standard treatment.

Final statistical analysis will be done after completion of all 144 patients.

When the upper boundary is passed, the study will be stopped prematurely and the use of rhTSH (with dosage and timing as in the protocol) can not become the standard treatment. Final statistics will be provided.

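### Passing the lower boundary is read as showing rhTSH is at least equal, but the boundary only limits the chance of a pass to about 10% when the true failure rate is 20%

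*Protocol*

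**What the plan says.** The Primary Objective asks whether the failure rate after rhTSH "is equal to the failure rate of I-131 therapy after endogenously stimulated I-131 ablation". The Study Design section describes stopping for inferiority or equality and gives the reading of the lower boundary: "If failure score after rhTSH passes the lower boundary than rhTSH stimulation is at least equal". Under Premature termination of the study, and again under Power analysis, the consequence of a lower pass is that "the use of rhTSH will become the standard treatment".

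The Power analysis sets the reference values: "a mean ablation failure rate up to 10% is considered acceptable", tested "with a rate of 20% as alternative". The upper-boundary settings are "constant alpha=0.014, cumulative alpha=0.05; beta =0.10". For the lower boundary the stated guarantee is that "with a true failure rate of 20%, the probability of passing the lower boundary is below 10" per cent. The subsection on the lower boundary calls it a bound for futile testing, after which monitoring may stop and H0 is accepted.

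Two further provisions matter. After a lower pass, the final analysis still waits for all 144 patients. The last part of the statistical section gives a point estimate and a 90% confidence interval for the failure rate after either boundary.

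**The concern.** The same event carries two meanings. In the statistical section, a lower pass means that continuing to test for inferiority is not worthwhile. In the Study Design section it is positive evidence of equality. Not rejecting a rate of at most 10% does not show that the rate is at most 10%.

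Equality with withdrawal is a further step. There is no concurrent withdrawal arm and no declared margin for equality; the reference is a fixed 10%. The Power analysis itself cites 80% success after withdrawal from a review (20% failure) and Dutch success rates from 56% to 93% (7% to 44% failure).

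At stake is the trial's headline conclusion and what is said to follow from it. The Introduction faults an earlier trial for calling a failure rate of 27% non-inferior to 7%. A lower pass here excludes about 20%, yet it would be reported as equality.

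**Working it through.** **Inputs (Power analysis and the boundary subsections).** p0 = 0.10; p1 = 0.20; N = 144; alpha(n) = 0.014, so Z = 2.197; alpha1(n) = 0.2638, so Z = 0.632; one look per patient.

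**Boundaries.**
- UB(n) = int{n·p0 + 2.197·√(n·p0) + 1}. At 144: 14.4 + 2.197 × 3.795 + 1 = 23.7, so UB = 23.
- LB(n) = int{UB(N) + 1 − p1(N−n) − 0.632·√(p1(N−n))}, not below 0. At 112: 24 − 6.4 − 1.6 = 16.0 (16.002 before rounding), so LB = 16 and a pass there has 15 failures. At 144, LB = 24, so 23 failures (23/144 = 16.0%) is the largest count that passes.

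**Method.** Exact forward recursion of the number of failures, with both boundaries active. The path stops upward when failures exceed UB(n) and downward when they fall below LB(n).

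**The protocol's own figures come first.**
- Upper pass at a true 10%: 5.08%. It is 4.98% with alpha(n) = 0.0138, which also rounds to 0.014. Stated: below 5%.
- Power at 20%: 89.9%. Stated: 90%.
- Median stopping point at 20%: 50 patients. Stated: 50.
- Median stopping point at 10%: 76 patients. Stated: 77.

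The formulas as written therefore reproduce the stated design closely.

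**Chance of passing the lower boundary.**

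| True failure rate | LB formula as written | LB(N) = UB(N) = 23 |
|---|---|---|
| 10% | 94.9% | – |
| 12% | 85.0% | – |
| 15% | 55.2% | 51.8% |
| 18% | 23.2% | – |
| 20% | 10.1% | 8.0% |

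Under the formula as written, the chance of passing is one half at a true rate of 15.4%. Varying alpha(n) from 0.0135 to 0.0145 moves the 15% entry only between 54.9% and 55.4%.

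**Why there is a second column.** The text on the lower boundary says the two boundaries coincide at N, but the formula gives LB(N) = UB(N) + 1 = 24. Taking them as equal shifts the median stop at 10% to 85 patients (stated 77), leaves the one at 20% at 50, and makes 22/144 the largest count that passes. At a true 15% it also leaves 1.9% of paths unresolved. The formula fits the stated medians better. The equal-boundary version fits the stated limit of below 10% better.

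**The plan's own interval after a lower pass.** The cumulative chance of a lower pass falls as p rises, so the value 0.05 gives the upper limit and 0.95 the lower; the protocol's text has these two reversed. In the right order, under the formula as written:
- 14/108: 8.6% to 19.9%
- 15/112: 9.0% to 20.2%
- 23/144: 10.0% to 21.4%, estimate 15.4%

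The upper limit is above 20% for every pass from n = 112 on. With LB(N) = UB(N), this starts at n = 130 (18 failures).

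**How often late passes occur.** Under the formula as written, a pass at n = 112 or later has probability 7.1% at a true 10%, 19.6% at 15% and 5.3% at 20%.

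**The case against.** The strongest reply is that the error rates are disclosed and deliberate. The Power analysis states both reference rates and both error levels, the statistical section names the bound as futility, and Figure 2 (not shown) covers true rates of 5% to 25%. About even odds midway between p0 and p1 is how any two-point test behaves, and 15% is an illustrative value, not a protocol threshold. All of this stands as a defence of the rule. It does not defend the reading given to a pass in the Study Design section.

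That section also says that even a statistically higher failure rate could be clinically acceptable. If so, a pass can be worded against a declared limit; calling it equality says something else.

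Three stronger readings are tempting and are not supported:
- **That the rule typically accepts about 16% failures.** 23/144 is the extreme. A stop there has probability 0.04% at a true 10% and about 0.5% at 15%. Passes up to n = 81 have at most 8 failures, under 10% observed.
- **That every pass is compatible with 20%.** This holds only for the late minority above; for earlier passes the plan's interval excludes 20%.
- **That allowing 10% for false acceptance and 5% for false rejection is an error.** It is a stated design choice. Preferring 5% is a preference.

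The protocol also has safeguards: the estimate and interval after stopping, and the analysis of all 144 patients after a lower pass. They soften the consequence, but neither is tied to the adoption statement.

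**Conclusion.** The concern holds as a matter of interpretation. A lower pass excludes a failure rate of 20% with a one-sided error of about 10% (10.1% by formula, 8.0% if the boundaries meet at N). It does not show a rate of 10% or less: a true rate of 15% passes with probability about 55% (52%). Without a withdrawal arm or a margin, it does not show equality with withdrawal either. In a minority of late passes, the plan's own interval would still include the 20% alternative while the conclusion read as equality.

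These figures assume the printed formulas, one look per patient, and independent patients with a common failure rate. The protocol calls its formulas approximations to be tuned, and Figure 1 is not shown. Exact crossing points are therefore less secure than the pass probabilities, which barely move. This should be fixed; it does not invalidate the design.

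**What to change.** 1. In Study Design, Premature termination and Power analysis, replace equality and at-least-equal as the reading of a lower pass with: a failure rate of 20% is excluded with a one-sided error of about 10%.
2. Require that any statement about adoption be accompanied by the planned estimate and 90% interval, with the limits in the right order, and by the planned analysis of all 144 patients.
3. Reconcile the lower boundary at N, where text and formula differ by one event, before quoting exact crossing points.

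A fixed patient number after which a pass would count as inconclusive is not recommended. Under the printed formula the last pass whose interval excludes 20% is at n = 108; with equal boundaries it is at n = 126. Cutting at 108 would lower acceptance at a true 10% from 94.9% to 87.9%, so it is a trade-off, not a correction.

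The cost is wording plus one clarified boundary value. No extra patients are needed. If the equal-boundary version is chosen, the stated stopping figures need recalculating.
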